### Setting

Target sites for implementation of DR screening and treatment in Thiruvananthapuram will include 16 FHCs for DR screening which represents the primary care centres where patients are screened for all complications of diabetes. The retinal images, captured by the trained, resident nursing staff will be sent to a newly developed reading centre at the Regional Institute of Ophthalmology, a tertiary care centre, where newly accredited graders will grade the images. Patients with screen-positive images will be referred to three secondary care hospitals (district hospitals). Severe cases that require complex interventions will be referred to the tertiary care centre, the tertiary for specialist management of DR.

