	Promote adaptability	Identify ways the DR care pathway can be tailored to meet local needs and clarify which elements of the pathway must be maintained to preserve fidelity.
	Provide clinical supervision	The Director of the tertiary centre will provide the overall clinical supervision of the whole DR care pathway. He will also delegate ophthalmologists to provide ongoing supervision for the optometrists involved in grading retinal images.
	Provide local technical assistance	Develop and use a system to deliver technical assistance focused on implementation issues using relevant service providers.
	Purposely re-examine the implementation	Monthly monitoring of screened patients at each family health centre, barriers observed and small changes that are required will be implemented to continuously improve the pathway.
	Remind clinicians	Primary care doctors in family health centres will receive monthly newsletter on the numbers recruited across all centres to highlighting successes and providing potential solutions to issues encountered.
Policy contexts	Issue Government of Kerala approval to enable dilatation of pupils of patients under supervision of family health centres doctors	Ensure doctors at family health centres receive approval for mydriasis in order to deliver the DR care pathway.
	Mandate change	The Health Secretary of State will provide leadership to ensure the prioritisation of the implementation of the DR care pathway.

ASHAs, accredited social health activists; DR, diabetic retinopathy; EHR, electronic health records; GCRF/UKRI, Global Challenge Research Fund/UK Research and Innovation.

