Adoption	Uptake of DR care pathway at primary, secondary and tertiary care. Uptake of training by staff. Uptake of screening programme by patients. Adoption of DR care pathway by the Government of Kerala for state-wide implementation.	*Assessment:* Proportion of staff at primary, secondary and tertiary care willing to integrate DR care pathway in their workload. *Data source:* Family health centres data and staff interviews. *Assessment:* Demand training sessions; attendance rates at training sessions. *Data source:* Number of training sessions and attendance registers at training sessions. *Assessment:* Increase in proportions of patient screened over 12 months. *Data source:* EHR and study database. *Assessment:* A policy paper by the Government of Kerala for state-wide adoption of the DR care pathway as part of diabetes care for all patients. *Data source:* A detailed scale-up plan will be developed for each district based on the clinical and cost-effectiveness data from this study to inform policy.
Appropriateness	Appropriateness of family health centres for DR screening. Appropriateness of the complex DR care pathway across primary and secondary care. Appropriateness of referrals to secondary care.	*Assessment:* Qualitative data on barriers and facilitators of the delivery of screening and treatment in secondary care. *Data sources:* Interview of staff at family health centres and secondary care, patient telephone survey on pathway from FHCs to secondary care. *Assessment:* False positive referrals from data collection at secondary care. *Data sources:* Study database; data from patient telephone survey.
Cost	Costs to the Government of Kerala and societal costs of the DR screening programme and subsequent treatment.	*Assessment:* Costs of the DR screening and treatment costs in total and per person, including the costs of staff training and cameras (suitably annuitised), staff costs and travel costs of patients. *Data sources:* Data collected in the study baseline and data from other services in India and from the literature.
Feasibility	Screening rate per family health centres. Barriers to monthly screening uptake.	*Assessment:* Monthly increase in numbers of FHCs added to the programme. *Data source:*Interview and monthly report from project manager on facilitators and barriers on each part of the pathway.

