Fidelity	Degree of the DR care pathway implementation. Validation of the DR grading within the telemedicine pathway. Delivery of training and the impact on the DR care pathway.	*Assessment:* Fidelity evaluation in 16 family health centres using a path-process analysis of the screening to identify the common screening pathway across centres. *Data source:* The path-process analysis will be based on detailed time-event logs of 70 patients from the 16 family health centres; a telephone follow-up of referred patients to evaluate uptake of referrals. *Assessment:* Validation of the DR grading will be assessed by the agreement of the DR grade reported by the optometrists at the reading centre in the tertiary centre and those reported by the ophthalmologists in the secondary care centres. *Data sources:* DR grading of referred patients obtained from the reading centre vs secondary care. *Assessment:* Increase in numbers of trained staff per month. *Data sources:* Staff interviews, structured observations and review of facility records. The proportions of doctors trained on laser delivery; data quality on the database; increase in non-communicable diseases registration following start of programme due to training of ASHA workers on diabetes and DR; increase in numbers of patients treated for STDR following training.
Penetration	Increase patient awareness of diabetes and DR and uptake of the DR screening pathway in patients with diabetes.	*Assessment:* Increase uptake of DR screening by patients registered in non-communicable diseases registers. *Data sources:* from non-communicable diseases register and EHR.
Sustainability	Policy makers to prepare policy on up-scale and sustainability plan for DR pathway. Integration of DR pathway in weekly activities in FHCs	*Assessment:* Availability of a policy paper from Government of Kerala on state-wide scale up of the DR care pathway. This will be considered a success of the programme. *Data sources:* Scale up plan for other districts including plan to purchase retinal cameras and acceptance of guidelines and training material for state-wide roll out. *Assessment:* Integration of DR pathway in EHR. *Data source:* EHR records of DR screening as part of non-communicable diseases care pathway.

ASHA, accredited social health activists; DR, diabetic retinopathy; EHR, electronic health records; FHCs, family health centres; STDR, sight-threatening diabetic retinopathy.

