### Statistical analyses

We will create a complete case data set of the cross-sectional survey for use in the analyses of effectiveness and assess the potential impact of missing data using sensitivity analysis incorporating a range of optimistic and pessimistic scenarios for the impact of missing data. We will model two outcomes that we hypothesised would be influenced by the intervention: (1) uptake of DR screening (primary outcome) and (2) numbers of patients referred for STDR as a result of screening. We will use bivariate logistic regression models to assess crude associations between sociodemographic factors such as age, gender, education, income and living arrangements, and other clinical data with DR and STDR and use fractional polynomials to account for the form of continuous covariates to predict uptake of DR screening. Factors associated with a p<0.25 will be candidates for inclusion in the multivariable logistic regression models. We will test interactions among identified main effects to capture improvement in model prediction assessed by reduced residual variance-based statistics. To account for the staggered entry into the study, we will add a variable indicating the month of entry of each FHCs into the programme (eg, 1. if the FHC join in the first month of the programme, 2. if in the second month and so on). A non-significant coefficient for this variable will suggest the staggered approach had no effect and a significant coefficient will allow the effect to be quantified for each FHC. In our final adjusted model, we will consider associations with a p<0.05 as statistically significant. Adequacy of model discrimination and calibration will be assessed using receiver operating characteristic curves. The validation of the telemedicine will be reported as the agreement (kappa statistics) between screen positive patients graded by the graders at the reading centre versus the DR grade as recorded by the ophthalmologists in secondary care centres. A kappa coefficient of 0.6 or higher was prespecified to indicate validity.

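### A kappa of 0.6 among screen-positive patients is read as validity of the telemedicine, although disease missed in screen-negative patients never enters it

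*Protocol article*

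**What the plan says.** Under Statistical analyses, the telemedicine is to be validated by one statistic: "agreement (kappa statistics) between screen positive patients graded by the graders at the reading centre versus the DR grade as recorded by the ophthalmologists". These ophthalmologists work at the district hospitals. The next sentence sets the criterion: "A kappa coefficient of 0.6 or higher was prespecified to indicate validity".

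Table 3 (Fidelity) lists the indicator as "Validation of the DR grading within the telemedicine pathway" and gives its data source as "DR grading of referred patients obtained from the reading centre vs secondary care". The Setting section explains why the two populations coincide: a screen-positive image is what sends a patient to the district hospitals.

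The one grading error that the outcome tables plan to count is in Table 3 (Appropriateness): "False positive referrals from data collection at secondary care". I found no reference grading of screen-negative patients anywhere in the article, and no sensitivity, false-negative rate or negative predictive value.

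**The concern.** This is partial verification. The reading centre's grade decides who receives the ophthalmologist's grade, so the agreement table has no entries for patients graded negative. Agreement among those referred is a sensible fidelity measure, but the plan draws a wider conclusion from it, namely that the telemedicine is valid.

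For a screening pathway the error that matters most is disease that goes unreferred. The article's Background says that STDR may cause no symptoms early on, so a missed patient may have no reason to come back. The results are also meant to inform state-wide adoption, and DR and STDR prevalence is to be estimated from the screened population. A validity statement that is silent on misses would lend both more support than the data give.

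**Working it through.** **The threshold.** The 0.6 is a chosen cut-off with no inputs, so there is nothing to reproduce. The question is what the statistic responds to.

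**Formula.** Unweighted kappa = (po − pe)/(1 − pe), where po is observed agreement and pe is the agreement expected from the margins.

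**Inputs.** From the Sample size section: DR 8%, STDR 3%. Assumed, because the article gives no grade distribution or error rates:
- five grades with true prevalences 92/3/2/2/1% (none, mild, moderate and two sight-threatening grades);
- a share of true DR graded as none, the same at every grade;
- the remaining DR graded exactly right with probability 0.85, otherwise in an adjacent DR grade (never none);
- reader grade moderate or worse counts as screen-positive;
- at first, no disease-free patient is graded positive.

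**Screen-positive kappa, no misses, per 10,000 patients.** The reader calls 530 positive, of whom 170 + 170 + 85 = 425 agree exactly. Ophthalmologist totals (mild, moderate, then the two higher grades) are 45/185/200/100; reader totals are 0/230/200/100.
- po = 425/530 = 0.802
- pe = (185×230 + 200×200 + 100×100)/530² = 92,550/280,900 = 0.329
- kappa = (0.802 − 0.329)/(1 − 0.329) = 0.705

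If half of all DR is missed, every cell of this table is halved. Proportions do not change, so neither does kappa.

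**Kappa over all patients.** With no misses, po = 0.92 + 0.85×0.08 = 0.988, pe = 0.848, kappa = 0.92. With 50% missed, po = 0.92 + 0.85×0.04 = 0.954, pe = 0.884, kappa = 0.60.

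| Share of DR missed | Screen-positive kappa | Kappa over all patients |
|---|---|---|
| 0% | 0.705 | 0.92 |
| 20% | 0.705 | 0.81 |
| 50% | 0.705 | 0.60 |
| 70% | 0.705 | 0.41 |

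**Adding false positives.** Suppose 5% of disease-free patients (460 per 10,000) are graded moderate. With no misses, po = 425/990 = 0.429, pe = (185×690 + 200×200 + 100×100)/990² = 0.181, kappa = 0.30. It falls to 0.19 with 50% missed and 0.13 with 70% missed, so the constancy above is particular to the first scenario.

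A low value is still ambiguous. Compare:
- no misses and 10% over-graded: 530 true and 920 false positives;
- 50% missed and 5% over-graded: 265 true and 460 false positives.

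The second table is the first with every cell halved, so both give kappa 0.19. One reading centre misses nothing and the other misses half of all DR.

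**Scale.** With 1131 screened and the article's own rates, about 1131×0.20 = 226 would be referred and 1131×0.03 = 34 would have STDR. At assumed sensitivities of 0.95, 0.80 and 0.60, about 2, 7 and 14 patients with STDR would be missed, and none of them would appear in the table.

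**The case against.** The case for leaving the rule alone has several parts.

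- **It is a minor outcome.** This is one of three Fidelity indicators. The primary outcome is the proportion screened, and no stated sample size or scale-up decision turns on this kappa. That stands, and it limits the weight of the point.
- **Other safeguards exist.** Graders are accredited, image quality and gradability are monitored, and Table 1 provides for supervision: "He will also delegate ophthalmologists to provide ongoing supervision for the optometrists involved in grading retinal images". These are real quality measures, but none of them estimates a miss rate.
- **The illustration is favourable.** It has perfect specificity and refers 5.3% of patients or fewer, against the roughly 20% that the article expects. Some of that 20% will be ungradable images or cataract, so the false-positive share is unknown. This stands: the example shows that the rule can pass a poor reading centre, not that it usually will.

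A reader might also infer more than the article supports:

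- That the statistic is blind to all missed retinopathy. It is not; under-grading within a referred patient lowers it.
- That kappa must be 0 because every patient analysed is screen-positive. That would hold for a refer/not-refer rating, but both passages compare DR grades.
- That a good reading centre would fail merely because the grade range is restricted. Nothing here shows that.
- That 0.6 is the wrong number, or that weighting and confidence limits have been neglected. The cut-off is not shown to be wrong, and an article may leave such detail to the full protocol or analysis plan.

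**Conclusion.** The point holds in a limited form. The article itself fixes the population, the statistic, the threshold and the conclusion, so this is not a detail deferred to another document. Followed as written, the plan can declare the telemedicine valid with no information on disease missed in patients graded negative.

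That the screen-positive table contains no screen-negative patient follows from the text and needs no assumption. The size does rest on assumptions: a kappa of 0.705 at 0%, 50% or 70% of DR missed, against 0.92, 0.60 and 0.41 over all patients, requires no false positives, misses equal across grades and 85% exact agreement on detected cases. With false positives the screen-positive kappa changes, but it does not identify the cause. The primary outcome is unaffected; what is unsupported is one prespecified conclusion.

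**What to change.** In Statistical analyses and in Table 3 (Fidelity), describe the measure as agreement on DR grade among referred patients who attended secondary care. Report it together with the proportion of referrals confirmed, which the false-positive count already planned in Table 3 supplies. Delete the statement that 0.6 indicates validity, or limit it to agreement in referred patients. This costs only wording; the downside is a narrower claim.

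Only if a validity claim is to be kept, and as an optional addition: have ophthalmologists re-read, masked, a random sample of screen-negative images, and weight the sample back to estimate sensitivity. The supervising ophthalmologists in Table 1 could do this, at the cost of extra reading time. It would measure sensitivity relative to an ophthalmologist's reading of the same image.

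The sample must be large enough to be useful. With zero misses found in n images, the one-sided 95% upper bound on the miss rate among screen-negatives is 1 − 0.05^(1/n): 3.0% for n = 100 and 1.0% for n = 300. Among about 1131 − 226 = 905 patients not referred, 1.0% still allows about 9 missed patients, against an expected 34 with STDR.

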### Patient and public involvement

A patient and public group will be involved in plans to disseminate the study results and provide their input on the scale-up of this DR care pathway, should the implementation in Thiruvananthapuram be deemed successful by the Government of Kerala.

## Ethics and dissemination

The study was approved by Indian Medical Research Council (2018-0551). The study complies with the guidelines of the Declaration of Helsinki. Results of this research are expected to be disseminated through stakeholder reports and via scientific forums, specifically peer-reviewed publications and conference presentations. All participants will give written informed consent prior to entry to the study by the FHCs nurses and will be made aware that participation is strictly voluntary.

## Discussion

At the conclusion of this study, we hope to assess the effectiveness and implementation outcomes of a complex DR care pathway integrating care at primary, secondary and tertiary care, covering a proportion of the diabetic population in Thiruvananthapuram. The study will set the scene for a policy for State-wide Screening and Treatment Pathway for Diabetes. Early identification of STDR and other complications due to this holistic approach and timely treatment are expected to have a positive impact on rates of blindness, chronic kidney disease, cardiovascular complications and thereby improve health, reduce multimorbidity and mortality. A DR pathway that straddles primary, secondary and tertiary levels of care, leveraging technology may have advantages of cost effectiveness and ease of implementation in LMICs compared with the current practice of detection and management of self-reported cases in tertiary centres.

This study outlines how the effectiveness of a DR care pathway and its implementation will be evaluated.^21 22^ This study is timely given the increasing numbers of people with diabetes and pressure on finances available for healthcare, necessitating task shifting to enable better coverage of the population. The study will also examine the organisation functions such as structure, resources and processes that would contribute to better outcomes. We will also examine whether this additional task is feasible given the current skill levels and workload of FHCs and secondary hospitals. The study will reveal whether current health seeking behaviour of patients will support screening, especially when an invasive procedure is requested when there is no obvious impact on quality of life of the patient. By addressing a key gap in knowledge due to lack of research in this area, we will be able to decipher the barriers and facilitators that influence the successful implementation of such a programme in the public system in India. The results of this study may inform the adoption of this pathway in other areas in India and globally. However, the complexity and number of implementation strategies, local contextual factors and lack of validated implementation outcomes may limit generalisability of the results and implementation of this pathway elsewhere.

There are limitations, however, to the study design. We do not have baseline data on DR screening in the study location as these screening programmes are non-existent. For this reason, we are examining the effectiveness of the pathway in terms of presenting visual acuity for referable cases as ‘proximal’ outcomes. In addition, when there is no concurrent control group, causal inferences are difficult to make and may lead to both measured and unmeasured biases. When examining implementation, logistical issues, variations in healthcare facilities, socioeconomic variation and quality of healthcare personnel may likely affect our study. However, the study design avoids the ethical challenges of having a control group with no DR screening. Therefore, the study design is by necessity non-randomised and observational and will rely on newly trained staff members to collect data, which is likely to differ in completeness between the 16 FHCs. We expect an increase in referral rates after implementation of the intervention due to better public awareness, increasing knowledge of ASHAs and improved case ascertainment, at least in some FHCs. We will also examine the impact of cataract in the community and this has not been studied before in any other DR pathway. We have tried to minimise the limitations by the use of robust statistical techniques and the use of various data sources to elicit a greater understanding of how the programme will lead to better health outcomes.

One of the strengths of this study is that quantitative data backed by qualitative data will be collected to strengthen our findings and enable generalisation of our findings. Second, we will use robust statistical methods to reduce bias including selection bias and other confounders. Finally, the access to and collaboration with the UK is a key strength of the study, as it facilitates the codevelopment of the interventions from the outset. Active involvement of policy makers engaged in transformation of primary care to screen for and address complications of non-communicable diseases who value research to generate evidence for policy making and who are prepared to learn from, and adapt the DR care pathway based on implementation experience is a unique feature of this study. Findings on the mechanisms and contexts that optimise the implementation of this complex multifaceted intervention using the ERIC taxonomy will be useful to those developing and implementing these programmes in other health systems. The health economic model may highlight the health expenditure required at individual, family and Kerala State level for forecasting and planning health budgets.

Perhaps the most important aspect of the chosen evaluation is that it is built within a simultaneous developing public health strategy on population-based screening of diabetes and hypertension and a recently introduced EHR called eHealth. Conducting research in such an environment is a good example of health policy and systems research.

Despite the limitations, this study holds promise for providing high-quality data and detailed implementation information on a complex intervention in a resources-limited setting. We hope to contribute to the literature on the implementation and effectiveness of DR screening and treatment in the public health sector in LMICs.
